## Abstract

**Background:**

Although effectiveness of web-based interventions on lifestyle changes are recognized, the potential of such programs on metabolic syndrome has not been explored. We describe the protocol of a randomized controlled trial that aims to determine the feasibility, acceptability, usability, and effectiveness of interactive technology on lifestyle intervention in a population with metabolic syndrome.

**Methods/design:**

This is a two-arm randomized controlled trial. The study includes 160 participants (n = 80 per arm) who will be recruited via online registration on the study website. The inclusion criteria are that they should have metabolic syndrome and have access to the Internet. All participants will receive information on dietary intake and physical activity through the study website. The intervention group will receive additional resources via the study website including interactive Healthy Heart Profile and calorie restricted diet tailored to the participants. The primary outcomes are feasibility, acceptability, usability, and the change in metabolic syndrome components. The secondary outcomes are comparing quality of life, physical activity and food intake among the study arms. The participants will be followed up to 6 months with data collection scheduled at baseline, 3 and 6 months.

**Discussion:**

There is a need for developing and evaluating web-based interventions that target people with high risk for cardiovascular diseases. This study will therefore make an important contribution to this novel field of research and practice.

**Trial registration:**

IRCT201111198132N1

## Background

Cardiovascular diseases (CVD) are the leading cause of mortality and morbidity worldwide and a growing health problem among developing nations [1, 2]. It is argued that metabolic syndrome is the most responsible risk factor for developing the disease [3–6]. The National Cholesterol Education Program Adult Treatment Panel (ATP) III defined metabolic syndrome as the presence of three or more of the following conditions: triglyceride level of at least 150 mg/dl, HDL level less than 40 mg/dl in men and less than 50 mg/dl in women, systolic/diastolic blood pressure 130/85 mm Hg or higher, fasting blood glucose level 110 mg/dl or higher and waist circumference greater than 102 cm in men and greater than 88 cm in women [7]. Metabolic syndrome is affecting about 20% of adult population without known diabetes and cardiovascular diseases and is associated with increasing cardiovascular morbidity and mortality [8, 9]. Ischemic heart disease was the leading cause of Disability-Adjusted Life Years (DALYs) worldwide in 2010 [10].

Recent evidence indicates that individuals with metabolic syndrome are approximately twice more likely to develop cardiovascular disease and between 3.5 and 5 times more likely to develop type 2 diabetes [11]. The prevalence of metabolic syndrome in Iran is very high. The Tehran Lipid and Glucose study (TLGS) reported that 42% of women and 24% of men were suffering from metabolic syndrome. Metabolic syndrome has been identified by central obesity, increased triglycerides, reduced high-density lipoprotein cholesterol (HDL), hypertension, and elevated fasting blood glucose concentration [12–14]. Increased cardiovascular mortality and metabolic syndrome morbidity in developing countries is largely due to the changes in lifestyle including changes in dietary habits and lack of exercise [15–17]. Therefore effective and affordable strategies to control the syndrome would benefit the at risk population.

In the past there have been several different strategies to fight metabolic syndrome. Although traditional lifestyle interventions such as face-to-face diet and exercise programs have succeeded in treating the metabolic syndrome [18, 19], clinical practice and research have shown significant difficulties with regard to availability, cost, treatment adherence and long-term efficacy of these procedures [20]. Indeed issues such as time and travel demands typically were identified as problems with traditional programs [21]. However, the new communication technologies provided alternatives that are becoming very popular. For instance the Internet penetration rapidly is growing and its use in medicine and health care are ever increasing. In particular web-based interventions has attracted a considerable attention as an approach in medical discipline.

A web-based intervention provides easily access to evidence-based content in every time and makes it feasible to increase tremendously the number of people reached to information [20, 22, 23]. According to Barak et al. a web-based intervention is: ‘a primarily self-guided intervention program that is executed by means of a prescriptive online program operated through a website and used by consumers seeking health- and mental-health related assistance’ [24]. The effectiveness of web-based interventions has been demonstrated for numerous health behaviors and chronic conditions. Review studies of web-based interventions reported positive results for smoking cessations [25–31], substance abuse [32], alcohol consumption [28, 33–39], weight management [20, 40–46], diabetes care [47, 48], depression, anxiety and stress [49–55], physical activity and nutrition [56–61] and chronic conditions [62, 63]. However, the effectiveness of these online applications is limited by high attrition rates and the fact that only few users visit a health intervention website more than once [64, 65]. In addition, it is argued although there is some evidence for the effectiveness of web-based interventions for improving healthy behaviors, it is clear that maintaining improvements remain a challenging issue [66].

There is evidence that among the web-based interventions for lifestyle changes those that benefit from interactive technology are more effective than those that provide one-way communications [66]. Interactive web-based technology is a two-way communication by which using the Internet, people could interact with provider. Interactive web-based technologies have several advantages. Access to credible information is quick and easy to read updated information [66]. Lower cost, better interaction, less time between screening and feedback are other returns of interactive web-based interventions [59, 67]. Interactive web-based programs can offer tailored information and messages to participants to personalize their experience and apply interventions in the privacy of their home and at the convenient time [23]. In fact by using interactive web-based technology one could design web-based interventions tailored to the need of target population. Therefore with the growth of new and exciting interactive technologies, opportunities to use this novel applicable approach is recommended to design easy to use, engaging, continual self-monitoring program for metabolic syndrome.

Internet penetration in Iran is 53.3% and 46.7% of people are using the Internet [68]. A recent study indicated that 32.7% of people living in Tehran (the capital) have used Internet at the past 12 months [69]. As any other communities the use of the Internet in Iran is rapidly increasing. However, in spite of that increase, we are not aware of any evaluation of web-based health programs conducted in Tehran, Iran.

### Aim

The aim of this randomized controlled trial (RCT) is to determine the feasibility, acceptability, usability, and effectiveness of an interactive web-based lifestyle intervention focusing on dietary and physical activity for reducing metabolic syndrome indicators. It was hypothesized that developing and launching an interactive web-based educational program would be feasible, acceptable and will be used by target audiences, and that using interactive web-based educational program will produce a change in lifestyle behaviors and this consequently will lead to reduction in metabolic syndrome.

## Methods

### Trial design

This study is an interactive web-based randomized trial (using pre and post-intervention assessments). Participants in this parallel study randomly will be assigned to one of two conditions: the intervention group and the waiting list group (the control group). Participants will be assessed at three points in time: at baseline, three and six months follow-up. Study procedure from enrollment through follow up data collection and analysis are depicted in Figure 1.

**Figure 1 Fig1:**
[figure not shown]
**‘Red Ruby’: the trial flow chart.**

### Study procedure

An interactive web page namely Healthy Heart Education (http://www.Heartresearch.ir) is designed in order to increase awareness of visitors about decreasing cardiovascular diseases and attract the attention of users for metabolic syndrome [Figure 2]. It is a free website providing information and advice about reducing heart diseases. This public website presents general information about hypertension, metabolic syndrome, diabetes, obesity and central obesity, nutrition for healthy heart and cardiovascular diseases (types, symptoms, prevention). The general educational materials are available in HTML and PDF formats. There is a registration page that invites people to take part in a study named the ‘Red Ruby’. The registration page includes recording of information on name, gender, age, waist circumference, weight, e-mail and address. The homepage also shows how to measure waist circumference.

**Figure 2 Fig2:**
[figure not shown]
**A snapshot of the website.**

### Recruitment

The study will be advertised by posters in virtual and non-virtual environments by announcing the web site address and indicating that people could visit the site for further information. Then those who visit the site will be invited to participate in the study by registering in the site. Accordingly the website’s database will be reviewed by a trained research assistance in order to identify registrant aged 20 and over living in Tehran (the study setting). Then, those who meet the study criteria will be contacted by the main investigator (LJ). Finally identified eligible participants who interested in pursuing the study, will ask to schedule for a free clinic visit and clinical measurements by a trained nursing staff at Tehran Heart Center.

### Participants

Participants are individuals that should have metabolic syndrome aged 20 years and above living in Tehran registered on the study website.

### Inclusion criteria

a) Waist circumference ≥ 90 (cut-off for metabolic syndrome in Iran for both gender [70–72]), b) Blood pressure ≥ 130/85, c) Access to Internet, d) Having simple skills to work with Internet

### Exclusion criteria

a) Having history of cardiovascular diseases, b) Diabetics, c) Having cancer, d) Patients with renal diseases, e) Being pregnant, f) Taking medication for hypertension, g) Taking medication for dislipidemia, and h) Having incomplete registration form

### Randomization

Randomization will be carried out after baseline measurements. Participants will be randomly assigned to the trial arms. Randomization sequence will created manually by a biostatistician using Excel software [Command in the Excel for random block sizes column: *=rand()*] [73] to assign participants to the study arms using a 1:1 allocation ratio with block size of 4. The allocation sequence will conceal from the investigators in sequentially numbered, opaque, sealed and stapled envelopes.

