### Intervention

Both intervention and control arms will be encouraged to engage in making healthy changes to their physical activity and nutrition behaviors in order to treat metabolic syndrome. The participants in intervention arm will be received the username and password to use the My Healthy Heart Profile and log-in to the interactive section of website. Participants in intervention arm will be encouraged to frequently log-in and visit their homepage or ask questions at any time they wish. For the security and confidentiality, the users will receive personal username and password. We will recommend the participants to keep the password safe and avoid sharing it with anyone. They will not able to change the password. If any one forgets the password a new one will be sent to his/her e-mails address.

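### Randomization describes block sizes both as random and as fixed at 4; if they are fixed, up to about a third of assignments could be known in advance to someone who knows the size and the earlier allocations

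*Protocol article*

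**What the plan says.** All references are to the protocol article.

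- **Randomization**, allocation rule: a biostatistician prepares the list in Excel "to assign participants to the study arms using a 1:1 allocation ratio with block size of 4".
- **Randomization**, bracket in the same sentence: "Command in the Excel for random block sizes column", followed by the `=rand()` function.
- **Randomization**, concealment and timing: "The allocation sequence will conceal from the investigators in sequentially numbered, opaque, sealed and stapled envelopes". Also: "Randomization will be carried out after baseline measurements".
- **Recruitment**: "those who meet the study criteria will be contacted by the main investigator". Those interested are then booked for a visit at one clinic, where nursing staff take the clinical measurements.
- **Intervention**: "The participants in intervention arm will be received the username and password" for the interactive profile. The description of the profile adds a tailored diet and answers to personal questions, both sent through the profile's inbox.
- **Control**: the other arm receives general e-mails every 3 weeks and has no access to the profile. Only control participants are described as unaware of their arm. No blinding of staff is described.

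**The concern.** There are two linked problems.

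First, the sentence names two schemes. Block sizes that vary at random and one size of 4 are different designs, and the reader cannot tell which was used.

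Second, if the fixed size is the operative one, it weakens the concealment that the envelopes are meant to give. Envelopes hide an unopened assignment. They do not stop someone working it out from the earlier assignments in the same block. The setting makes this more than theoretical: one clinic, one undivided list, and logins, diets and e-mails that differ visibly by arm, so at least the staff who deliver the intervention learn allocations once they are made.

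At stake is selection at entry. A foreseen assignment can influence who is booked and in what order. Blood pressure is an entry criterion read by an observer and is also a component of the primary outcome, so the baseline reading could be influenced too. Later analysis cannot reliably remove bias of this kind.

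**Working it through.** **Inputs from the article.** Allocation 1:1 and block size 4 (Randomization); 160 participants, 80 per arm (Abstract). This gives 160/4 = 40 complete blocks. The article gives no predictability figure to reproduce.

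**Assumption for the upper case.** The guesser knows the block size, where blocks begin, and every earlier allocation in order.

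**Assignments known with certainty, fixed size 4.** A block holds two A and two B, so there are 4!/(2!·2!) = 6 equally likely sequences.

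- AABB and BBAA: the last two assignments are forced.
- ABAB, ABBA, BAAB and BABA: only the last is forced.

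Expected number per block = (2×2 + 4×1)/6 = 8/6 = 1.333. As a share, 1.333/4 = 33.3%. Over 40 blocks this is 53.3 assignments on average, with a possible range of 40×1 = 40 to 40×2 = 80.

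**Best-guess accuracy, fixed size 4.** The guesser always names the arm with fewer assignments so far. The chances of being right at positions 1 to 4 are:

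- 1st: 1/2
- 2nd: 2/3
- 3rd: (2/3)(1/2) + (1/3)(1) = 2/3
- 4th: 1

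The sum is 17/6, and (17/6)/4 = 17/24 = 70.8%.

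**The same quantities with randomly varying sizes.** The article names no set of sizes, so those below are assumptions. The sizes in each set are equally likely, and the guesser knows the set but not the realised sizes. Results come from 1,500 simulated trials of 160 participants per set.

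| Block sizes | Known with certainty | Best guess correct |
|---|---|---|
| 4 (fixed) | 33.3% | 70.8% |
| 2, 4 | 11.1% | 72.2% |
| 4, 6 | 5.5% | 69.2% |
| 2, 4, 6 | 4.2% | 70.2% |
| 4, 6, 8 | 2.2% | 68.0% |

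For sizes 4, 6 and 8, 2.2% of 160 is about 3.6 assignments.

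**Analytic check of the last row.** For a block of size 2m, naming the arm with fewer assignments gives m + (4^m/C(2m,m) − 1)/2 correct guesses on average:

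- m = 2: 2 + (16/6 − 1)/2 = 2.833
- m = 3: 3 + (64/20 − 1)/2 = 4.100
- m = 4: 4 + (256/70 − 1)/2 = 5.329

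The total is 12.262 correct out of 4 + 6 + 8 = 18, or 68.1%, which agrees with the simulation. Accuracy hardly changes because this strategy needs only the running totals per arm, not the block size.

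**Imbalance.** The largest imbalance if recruitment stops mid-block is half the largest block: 2 with blocks of 4, and 4 with blocks up to 8.

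**The case against.** **Knowledge of earlier allocations is not documented.** A reader might infer that the study team knows the past allocations and that a third of assignments are therefore predictable in practice. The article does not support this. It says the sequence is concealed from the investigators, does not say who issues the logins, has a dietitian provide the diets, and says of the main investigator only that this person contacts eligible registrants. Knowing some allocations after the fact is not the same as knowing all of them in order with the block boundaries. Nor does the article show that recruiters could read the block size during enrolment. This objection stands, and it makes one third an upper case.

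**The bracket may be loose wording.** `=rand()` returns a random number, not a block size, so the bracket may mean the column used to order assignments within blocks of 4. If so, the conflict is one of wording only, but the fixed size of 4 remains. If varying sizes are in fact operative, the one-third figure does not apply and certain knowledge is roughly 2% to 11% for the sets tried. The two readings cannot be charged together.

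**Safeguards exist.** Randomization follows baseline measurement, and the waist and blood-pressure criteria are numeric. This narrows selective entry but does not cover the order of booking or an observer-read blood pressure.

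**The scheme is conventional, and a condensed article omits operational detail.** Silence on who opens the envelopes is no finding. The stated fixed size, and its conflict with the bracket, are on the page.

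**Conclusion.** The concern holds in conditional form. The wording conflict is certain. The arithmetic is exact: with blocks fixed at 4, full knowledge of the size and of the earlier allocations in order reveals 33.3% of assignments on average (about 53 of 160). That this applies to anyone who recruits is not stated, so the figure bounds the exposure and does not describe what happened. There is no evidence in the article of actual selection bias.

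A reader might also set the 70.8% best-guess accuracy against 50% for a coin toss and take the difference as the gain from changing the scheme. That contrast should not be used: blocks of 4, 6 and 8 still give about 68%. The gain lies in certain knowledge, from 33.3% to about 2%, and depends on the realised sizes being unknown to the guesser.

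The change is worth making because it is cheap and replaces a stated rule that weakens concealment in a trial with no stated blinding of staff.

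**What to change.** 1. Reconcile the two statements in Randomization so that only one scheme is described.
2. For assignments still to be made, use permuted blocks of randomly varying size, for example 4, 6 and 8, generated by the biostatistician. Delete the fixed size of 4.
3. Withhold the sizes from everyone who contacts, enrols or measures participants.
4. Save the list as fixed values before the envelopes are filled, because `=rand()` recalculates.
5. If enrolment is complete, correct the Randomization text and report which scheme was used and who knew the block size.

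Cost: regenerating the list and refilling any unused envelopes. The possible imbalance if recruitment stops mid-block rises from at most 2 to at most 4 participants, which is small against 80 per arm. If enrolment is over, the cost is a text correction.

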### Intervention

Both intervention and control arms will be encouraged to engage in making healthy changes to their physical activity and nutrition behaviors in order to treat metabolic syndrome. The participants in intervention arm will be received the username and password to use the My Healthy Heart Profile and log-in to the interactive section of website. Participants in intervention arm will be encouraged to frequently log-in and visit their homepage or ask questions at any time they wish. For the security and confidentiality, the users will receive personal username and password. We will recommend the participants to keep the password safe and avoid sharing it with anyone. They will not able to change the password. If any one forgets the password a new one will be sent to his/her e-mails address.

### My healthy heart profile

My Healthy Heart Profile is an interactive web-based program designed for reducing metabolic syndrome. The program is developed according to the ‘feedback and monitoring’ as a behavior change technique [74]. It is designed to send feedback to each participant according to his/her metabolic syndrome indicators. In fact the participants will receive text-based messages and graphic feedbacks immediately after compellation of each records of risk factors.

My Healthy Heart Profile is structured in six parts and includes:Personal home page: on the main page educational materials will be uploaded every 2 weeks. The titles are: Do you know your cholesterol level?, Control your high blood pressure, Are you at risk for heart disease, Do you need to lose weight?, Protect your heart against diabetes, Physical activity and your heart, and Lowering blood pressure. Users can download and read all educational materials or save and print to read it at convenient time.Personal information includes name, age, gender, weight, height, telephone number, and e-mail address.Inbox as an interactive section in the profile for personal questions. Participants in intervention arm can send personal questions and receive answers. We will send a calorie-restricted tailored diet to all participants’ inbox provided by a dietitian. The calorie restricted diet will be based on each participant’s calorie requirement according to his/her ideal body weight (IBW) and corrected body weight (CBW) with less than 30% of calories derived from fat, in accordance with the National Heart, Lung, and Blood Institute guidelines [75]. IBW will be calculated with Hamwi equation [76]. CBW is defined as ((IBW + 25% (actual body weight – IBW)). We will request from intervention group to adhere the dieting program.A cardiovascular risk estimation tool for 10-years (based on the Persian online version of Framingham Risk Score-FSR). The FSR considers six cardiovascular risk factors, including age (over than 20), gender (male and female), total cholesterol (TC), HDL-cholesterol, systolic blood pressure, and smoking habits. This section is an interactive tool for users to calculate the heart attack risk score in every log-in and obtain feedback via the text by the three traffic lights that are illustrated for three levels of risks (high, moderate and low risk). If the estimation of risk was over 20%, red light will bright and for risk between 10 to 20% and less than 10% orange and green light will turn on respectively. Users will receive an explanation regarding their score and will be guided to educational materials on the personal homepage.Anthropometric and clinical measures: in this section user will record periodic measurements of weight, waist circumference, BMI and blood pressure, Total cholesterol, LDL-cholesterol, HDL-cholesterol, triglycerides, and Fasting blood glucose. These measurements will be displayed in a simple graph with three warning color (red = needs attention, orange = close to risk and green = good) for each recording. The risk factors will draw at the sequence diagram automatically and will show level of risks for individual separately.The questionnaires: users will complete a set of study questionnaires.
